## Discussion

This study protocol presents the design of a cluster randomised controlled trial testing the efficacy of a SRE lesson intervention to increase young adults’ condom use intention and behaviour through enhancing chlamydia risk and coping appraisals. As far as the authors are aware, this is the first controlled trial testing the efficacy of an intervention to increase condom use intentions and behaviour through modifying chlamydia risk appraisals, and one of few studies to accurately test the motivational hypothesis in the context of precautionary sexual behaviour.

A limitation of this study is that sexual behaviour will be measured by self-report. Clearly the use of self-reported condom use is unavoidable given the sensitive and private context of the behaviour. Test-retest reliability analyses and validation of self-reports against reports from sexual partners suggest however that, despite the potential for biased reporting, self-report measures of condom use do have satisfactory reliability and validity [29-31]. A further limitation of this study is the focus on chlamydia risk appraisal in isolation. Evidence suggests that other sources of perceived risk, such as the risk of pregnancy are likely to be driving intentions to engage in protective sexual behaviour [20]. This study therefore does not examine or account for, the relative contribution of other sources of risk which may be equally or more powerful predictors of intention. Finally it should be noted that there is a follow-up period of only two months. Whilst a short-term follow-up is typical of trials evaluating the efficacy of sexual health behaviour change interventions [32] it means that long-term efficacy will not be established by this study.

If the intervention is effective in increasing risk appraisal, response efficacy or self-efficacy, this study will provide important information about which behaviour change techniques can be used to bring about favourable changes in these behavioural determinants for precautionary sexual behaviour. If the intervention is effective in changing condom use intentions or behaviour, then it can be recommended for widespread distribution within schools. It also has the potential for use within alternative contexts such as by the National Chlamydia Screening Programme (NCSP) to encourage uptake of screening invitations. If the findings of the proposed study support the motivational hypothesis, then this will support the continued inclusion of risk appraisal within theories of health behaviour change.

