### Research questions

#### Primary research question

•Is the lesson effective in increasing young people’s *intentions to use* condoms during vaginal sex with casual sexual partners?

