## Methods/design

A two-arm cluster randomised controlled trial (RCT) using a waiting-list control will be used to test the efficacy of an intervention to increase young adults’ intentions to use condoms and actual use of condoms with casual sexual partners compared to a control group (see Figure 1). Secondary school pupils will be invited to participate. The intervention is a single lesson on chlamydia which aims to increase young adults’ chlamydia risk and coping appraisals. We hypothesise that there will be an increase in condom use intentions following delivery of the chlamydia lesson. At the two month follow-up, we hypothesise that there will be a higher rate of condom use during vaginal sex with casual sexual partners amongst sexually experienced participants in the intervention group compared with the control group. At two months, we will also measure condom use intentions to see whether any increases have been maintained over time. We hypothesise any effects of the intervention on condom use intentions or behaviour will be mediated by risk appraisals and/or coping appraisals.

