### Sample size calculation

The calculation is based on the primary research question. Power analysis using GPower 3.1.2 has indicated that 484 participants will provide 95% power to detect a small to medium effect of 0.3 [21] where α = 0.05. The effect size of 0.3 is based on a recent meta-analysis examining the effectiveness of interventions in changing risk appraisals, intentions and behaviour [22]. Due to the tendency for individuals within a cluster to be more similar to each other than those in other clusters, it is necessary to make adjustments to avoid an overestimation of power [23]. In order to obtain this adjusted sample size, the sample size determined by usual procedures is inflated by multiplication with a factor. This factor is known as the “design effect” and is calculated as:

$$1+\left(n–1\right)\mathrm{ICC}$$

where *n* is the average cluster size, and ICC is the intraclass correlation coefficient. The ICC for intention to use condoms between schools is not known but an estimate of 0.01 is reasonably conservative [23]. With ten schools and an average cluster size of 60 (×2 classes of 30 pupils), the design effect is:

$$1+\left(60–1\right)0.01=1.59$$

Accordingly the adjusted sample size is 484 × 1.59 = 770. We will over-recruit to allow for drop-out between the start of the study and the three month follow-up.

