### Outcomes

#### Primary outcome

Intention to use condoms during vaginal sex with casual sexual partners over the next two months.

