#### Secondary outcomes

Use of condoms during vaginal sex with casual sexual partners over two months post delivery.

Perceived likelihood of chlamydia.

Perceived severity of chlamydia.

Response efficacy for condom use.

Self-efficacy for using condoms during vaginal sex with casual sexual partners over the next two months.

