#### To examine the effect of the intervention

Analysis of Covariance (ANCOVA) will be performed to examine differences in condom use intentions (at time two and at follow-up), and behaviour. This will control for demographic variables (gender, ethnicity, age), behaviour at time one, and measures of risk appraisal, and coping appraisal.

If the lesson is effective in increasing condom use intentions, mediation analysis [28] will be conducted to identify whether changes in risk appraisals and/or coping appraisals are responsible for this change. This will help to identify the mechanism of change and indicate where future research and/or resources should be focussed.

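### The recommendation to distribute the lesson may rest on intentions or behaviour, but intention is the only primary outcome and the only one to which the stated alpha of 0.05 is tied

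*Protocol article*

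**What the plan says.** All references are to the protocol article.

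- **Primary research question:** "Is the lesson effective in increasing young people’s *intentions to use* condoms during vaginal sex with casual sexual partners".
- **Primary outcome:** "Intention to use condoms during vaginal sex with casual sexual partners over the next two months". This gives the period the intention refers to, but not the assessment (post-lesson or follow-up) at which the primary comparison is made.
- **Secondary outcomes:** "Use of condoms during vaginal sex with casual sexual partners over two months post delivery", together with four appraisal measures.
- **Sample size calculation:** "The calculation is based on the primary research question", and "484 participants will provide 95% power to detect a small to medium effect of 0.3 [21] where α = 0.05". No other section gives a significance level, and whether the level is one- or two-sided is not stated.
- **Methods/design, opening paragraph:** "We hypothesise that there will be an increase in condom use intentions following delivery of the chlamydia lesson". The same paragraph treats intention at follow-up as a check that any gain has lasted, and states the behaviour hypothesis for sexually experienced pupils.
- **To examine the effect of the intervention:** the planned comparisons are given in one sentence, which reads "Analysis of Covariance (ANCOVA) will be performed to examine differences in condom use intentions (at time two and at follow-up), and behaviour".
- **Discussion, last paragraph:** "If the intervention is effective in changing condom use intentions or behaviour, then it can be recommended for widespread distribution within schools".

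**The concern.** Naming one primary outcome controls the false-positive rate of a trial's conclusion only if the conclusion depends on that outcome. Here the Discussion joins intentions and behaviour with an *or*. A favourable result on a secondary outcome would then support wide distribution on the same terms as a favourable result on the primary.

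Intention itself also offers two chances, because it is analysed at two time points and neither the outcome definition nor the analysis section says which one decides. The maintenance role given to follow-up intention in Methods/design is not carried into the analysis sentence or the recommendation.

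At stake is the trial's main practical claim. A recommendation to schools could be made at a higher false-positive rate than the level planned for the primary question, including in a trial where post-lesson intention did not differ significantly between arms.

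**Working it through.** **1. The plan's own figure.** Inputs from Sample size calculation: effect 0.3, power 95%, alpha 0.05, total 484. The normal approximation per arm is n = 2(z_alpha + z_power)² / 0.3².

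- One-sided 0.05: 2(1.645 + 1.645)² / 0.09 = 240.5, so 241 per arm and 482 in total. The exact t calculation gives 484, with power 95.06%.
- Two-sided 0.05: 2(1.960 + 1.645)² / 0.09 = 288.8, so 289 per arm and 578 in total. The exact t calculation gives 580, and 484 would then have 90.9% power.

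The stated 484 is reproduced only with one-sided alpha, so the plan's arithmetic puts the whole 5% in the favourable direction. The text does not say so.

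**2. Contrasts that could satisfy the Discussion's wording.** There are three on the broad reading: post-lesson intention, follow-up intention and condom use. There are two if follow-up intention is only a maintenance check.

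**3. Chance of at least one false favourable result when the lesson has no effect.** For k independent tests, each with favourable-direction error a, this is 1 − (1 − a)^k. For correlated tests it is one minus the multivariate normal probability that no statistic exceeds its critical value. The protocol gives no correlations, so those below are assumed.

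*One-sided 0.05 per test (a = 0.05)*

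- Three independent: 1 − 0.95³ = 14.3%, which is 2.85 times 5%.
- Three, with correlation 0.5 between the intention contrasts and 0.3 with behaviour: 12.6%.
- Three, all correlations 0.5: 11.8%.
- Three, all 0.7: 10.3%.
- Three, all 0.9: 8.0%.
- Two independent: 1 − 0.95² = 9.75%, the ceiling for non-negative correlation. At correlation 0.3 to 0.5 it is about 9%.

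*Two-sided 0.05 per test, favourable results only (a = 0.025)*

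- Three independent: 1 − 0.975³ = 7.3%.
- Three, all correlations 0.5: 6.3%.
- Three, all 0.9: 4.2%.
- Two: 1 − 0.975² = 4.9% if independent, falling to 3.5% at correlation 0.9.

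The single-test reference is 5% in the first set and 2.5% in the second. In every case the rate exceeds its own reference. In the second set, the two-contrast rate stays below 5%.

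**The case against.** The strongest reply is that the protocol does rank its outcomes. Intention is primary, behaviour is secondary, alpha and power belong to the primary question, and Methods/design treats follow-up intention as a maintenance check. The Discussion sentence is narrative: it says the lesson can be recommended, sets no threshold and does not define effectiveness. No section states that each contrast is tested at 0.05, and a testing order may sit in an analysis plan not shown.

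Much of this stands. The absence of a multiplicity procedure from an article is not a fault in itself, and the per-test level used above is an assumption. What remains is a statement the article does make. It is the only place that says which result would support distribution, and it puts a secondary outcome on a level with the primary. A hierarchy held elsewhere would conflict with that wording.

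Two stronger readings are tempting and are not supported.

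- *A reader might infer that the false-recommendation rate is about 2.5 times the stated 5%.* With two-sided tests, three contrasts and correlation 0.5, the chance of any significant result is 12.5%, but this counts results against the lesson, which could not lead to a recommendation. Counting only favourable results gives 6.3%, or 1.26 times 5%. A multiple near 2.5 needs one-sided tests, three contrasts and moderate correlation, none of which the protocol fixes.
- *A reader might infer that most false recommendations would come without a significant post-lesson intention result.* With one-sided tests and all correlations 0.5 the share is (11.8 − 5.0)/11.8 = 58%, but at 0.9 it is (8.0 − 5.0)/8.0 = 37%. With two equal-level contrasts it is always below half.

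**Conclusion.** The concern holds as a mismatch between the stated basis for recommending the lesson and the single outcome to which alpha is tied. The missing time point in the primary outcome definition makes it worse.

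Its size depends on how the tests are run. If they follow the one-sided level implied by 484, the false favourable rate lies between 8% and 14.3% for three contrasts, and is at most 9.75% for two. If they are two-sided at 0.05, it is about 4-7% for three or 3.5-4.9% for two, against 2.5% per test. On the mildest reading (two contrasts, two-sided tests) the rate does not exceed 5%, so a large inflation cannot be asserted from the document. All figures assume that each single test is otherwise valid.

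**What to change.** - **Primary outcome** and **To examine the effect of the intervention:** name the between-arm difference in post-lesson intention as the single primary contrast at alpha 0.05. This matches the first hypothesis in Methods/design.
- **Same analysis section:** either test follow-up intention and condom use only after a significant primary result, in a fixed sequence, or report them as supportive. The order within a sequence is the authors' choice.
- **Discussion:** make the recommendation depend on the primary contrast, and say that an isolated effect on follow-up intention or behaviour is exploratory.

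The cost is wording only: no extra pupils or data, and no loss of power for the primary contrast, which keeps the full alpha. The downside is that a follow-up or behaviour effect without a primary effect could not by itself support distribution.
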